**4.1 Timing of Registration and Randomization to Study**

Eligible patients will sign the informed consent form to agree to participate in the study. The randomization should be completed at least one working day in advance of the planned operation date. No more than 14 days must elapse between the date of treatment randomization and the date of operation. The interval between Day 1 of the last cycle of neoadjuvant chemotherapy and randomization to the study could be no more than 8 weeks (2 months).

The study monitor will notify the investigator by electronic mail, within a period of one working day, of the patient study number and treatment arm to which she has been randomized. This study is unmasked, and all patients, investigators and surgeons will be aware of the study group assignment.

The administrative coordinator of the study registered all selected patients before beginning the operation. Patients who were not registered before the operation will not be permitted to participate in the study.

**4.2 Treatment Groups**

Patients will be assigned by the randomization system to one of the following groups:

- UC group: ultrasound-assisted CNS.
- GC group: CNS plus ICG dual-tracer-guided.

**5. PATIENT TREATMENT**

**5.1 Preoperation Chemotherapy**

Standard neoadjuvant therapy before randomization will be performed according to the NCCN guidelines and clinical practice.

Evaluation of neoadjuvant chemotherapy (every 2 cycles):

- Breast and axillary ultrasound (every 2 cycles)
- Mammogram (first plus one before surgery)
- Breast MRI (first plus one before surgery)

Quality control of SLNB after neoadjuvant therapy entails removal of the clip-containing node and at least 3 lymph nodes. Intraoperative radiography will be used to identify the clipped node.

**5.2 Procedures**

After completing preoperative radiographic evaluation, participants/patients will proceed to surgery for SLNs mapping. Excision of the primary tumor will be performed at the same time and in the same setting.

**Experimental arm (****UC group):**

One milliliter of CNSs will be subcutaneously injected into the areolar area in the upper outer quadrant of the breast. The injection site will be massaged for 15 minutes to promote drainage of the tracer into the axilla. During the intraoperative ultrasound-assisted procedure, an ultrasound diagnostic system will be used. Before making the incision, ultrasound-guided exploration of the SLNs will be performed by placing the probe on the lateral border of the breast and sliding it cranially along the lateral border of the pectoralis major muscle. A sterile skin marker will be used to mark the optimal site of incision over the targeted lymph nodes, and the distance from the skin to the nodes will be measured by ultrasound and recorded in millimeters. Blunt dissection is carried out to identify the CNS-stained nodes around the marked region. An ultrasonography probe is placed repeatedly in or around the wound at different angles for adequate visualization if the SLNs could not be localized with further dissection. All black-stained lymph nodes or suspicious lymph nodes will be excised.

**Control arm (GC group):**

One milliliter of CNSs will be subcutaneously injected into the areolar area in the upper outer quadrant of the breast. The injection site will be massaged for 15 minutes to promote drainage of the tracer to the axilla. One milliliter of diluted ICG (2.5 mg/ml) will be subsequently injected into the areolar area in the upper outer quadrant of the breast. A fluorescence tracer system will be used to visualize the subcutaneous lymph vessels and localize the SLNs. All fluorescent or black-stained lymph nodes along with any suspicious nodes will be removed. The remaining surgical field will be reexamined to ensure complete resection of the fluorescent lymph nodes.

An SLN number will be collected immediately following excision of each lymph node:

- A sentinel lymph node is defined as any lymph node that is either “fluorescent” and “black”, “fluorescent” only, “black” only, or a palpable suspicious lymph node.
- A “fluorescent” SLN is defined as a node that emits fluorescence under near-infrared camera detection.
- A “black” SLN is defined as any lymph node that is visibly stained black, has a visible contiguous black-stained afferent lymphatic, or both.
- Digital palpation (for the detection of intraoperatively clinically grossly suspicious (i.e., enlarged or hard) lymph nodes) will also be conducted.

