**5.4 Intra-operative Frozen Section of Lymph Nodes**

All removed lymph nodes will be sent for intraoperative frozen section analysis and pathology for further evaluation. Prior to any pathological evaluation, confirmation of ex vivo counts per tissue should be conducted. The pathological evaluation of the lymph nodes will include serial sectioning with H&E staining as well as IHC stain.

- In those cases in which intraoperative frozen section analysis is performed and all SLNs are found to be negative for malignancy on intraoperative frozen section evaluation, no further removal of axillary lymph nodes will be undertaken, unless otherwise determined as necessary at the discretion of the operating surgeon.
- In those cases in which intraoperative frozen section analysis is performed and the SLNs are determined to be positive for malignancy on intraoperative frozen section evaluation, a formal axillary lymph node dissection (levels I and II) may be performed at the discretion of the operating surgeon, or may be excluded at the discretion of the operating dissection (as based upon the ACOSOG Z0011 criteria).
- Any axillary lymph node that is neither “fluorescent” nor “black” but is determined to be intraoperatively clinically grossly suspicious (i.e., enlarged or hard) will also be removed. In those cases in which any clinically grossly suspicious lymph nodes removed intraoperatively are determined to be positive for malignancy on intraoperative frozen section evaluation, a formal axillary lymph node dissection may be performed at the discretion of the operating surgeon.
- In those cases in which no SLN can be intraoperatively identified at the time of the SLNB procedure, formal axillary lymph node dissection may be performed at the discretion of the operating surgeon.

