**6.3.2 Analysis of Primary Variables**

The primary endpoint is the identification rate of the SLNs, defined as the number of patients who had at least one SLN detected divided by the total number of patients included. Quantitative variables will be expressed as percentages. The 95% confidence interval will be calculated.

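### The only sentinel-node definition admits a palpable suspicious node with no tracer signal, so some tracer failures can count as successes on the primary endpoint

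*Protocol*

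**What the plan says.** The protocol defines an SLN once, in section 5.2 under the control-arm heading. Four kinds of node qualify: both fluorescent and black, fluorescent alone, black alone, "or a palpable suspicious lymph node". The fourth needs no tracer signal. The same list adds palpation as a detection step: "Digital palpation (for the detection of intraoperatively clinically grossly suspicious (i.e., enlarged or hard) lymph nodes) will also be conducted".

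Suspicious nodes are removed in both arms. For the UC arm: "All black-stained lymph nodes or suspicious lymph nodes will be excised". For the GC arm: "All fluorescent or black-stained lymph nodes along with any suspicious nodes will be removed". The UC text has no SLN definition of its own.

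Section 6.3.2 defines the primary endpoint as the identification rate, "defined as the number of patients who had at least one SLN detected divided by the total number of patients included". It does not require the detected node to be stained or fluorescent, and neither does the synopsis.

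Section 5.4 gives a node with neither signal its own bullet, saying that such a node "but is determined to be intraoperatively clinically grossly suspicious (i.e., enlarged or hard) will also be removed". That bullet stands apart from the bullets on SLN results and from the one on patients in whom no SLN is found.

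**The concern.** The trial asks whether ultrasound with carbon nanoparticles (CNS) locates sentinel nodes as well as CNS plus indocyanine green. Finding an enlarged or hard node by touch depends on neither method. If it counts as identification, a patient in whom the assigned method found nothing can still be scored as a success for that method.

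In a superiority trial, dilution of this kind would work against the new method. In a non-inferiority trial it works in its favour: moving part of the failures in both arms to success shrinks any real deficit and makes the 6-point margin easier to meet. The call is made during surgery by an unmasked surgeon (section 4.1). The same nodes also add to the number of SLNs collected, a secondary endpoint.

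Separately, sections 5.2 and 5.4 do not sit together. Under 5.2 an unstained suspicious node is an SLN; 5.4 handles it as a different class. Two assessors could score the same patient differently.

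**Working it through.** **Inputs from the protocol (section 6.3.5; allocation from section 4).** Identification rate 96% in each arm, margin 6 points, one-sided alpha 0.05, power 80%, 264 evaluable patients, 294 recruited after 10% dropout, 1:1 allocation.

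**Input not in the protocol.** r, the share of tracer failures in which a palpable suspicious node is removed and counted. I take a range of 0 to 50%.

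**Step 1: the plan's own figure.** n per arm = (1.645 + 0.842)² × 2 × 0.96 × 0.04 / 0.06² = 131.9, so 132 per arm and 264 in total. With dropout, 264 / 0.9 = 293.3, so 294. Both match. The sample size is not at fault.

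**Step 2: effect of the definition, applied to both arms.** If t is the tracer-only rate, the observed rate is t + (1 − t) × r. The observed difference is then the true difference × (1 − r).

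**Step 3: false non-inferiority at the margin.** Take true tracer-only rates of 96% (GC) and 90% (UC), a deficit of exactly 6 points. The probability of declaring non-inferiority comes from exact binomial enumeration at one-sided 5%. The protocol does not name a test, so each range runs from the score test (restricted maximum likelihood) to the Wald test.

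| r | GC | UC | Deficit (points) | 147 per arm | 132 per arm |
|---|---|---|---|---|---|
| 0 | 96.0% | 90.0% | 6.0 | 4.6-6.3% | 4.6-6.1% |
| 10% | 96.4% | 91.0% | 5.4 | 7.0-9.6% | 6.9-9.0% |
| 25% | 97.0% | 92.5% | 4.5 | 12.9-17.6% | 12.5-16.3% |
| 50% | 98.0% | 95.0% | 3.0 | 34.7-44.4% | 32.2-41.3% |

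The Wald test already exceeds 5% at r = 0, so each row should be compared with the r = 0 row rather than with a flat 5%.

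**Step 4: equal true rates.** If both arms are truly at 96% and r is the same in each, the observed difference stays zero and is unbiased. Only power changes (normal approximation, 132 per arm): 80% at r = 0, 83% at 10%, 89% at 25%, 97% at 50%.

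**Step 5: definition applied to the GC arm only.** The bias reverses. At true 90% v 96% and r = 25%, the observed rates are 97.0% v 90.0%, a 7.0-point deficit. False non-inferiority falls to 2.1-3.2% (147 per arm). At equal true rates of 96%, power falls from 80% to 71% (132 per arm, normal approximation).

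**The case against.** The strongest reply concerns size. Section 3.1 admits patients who are cN0 or downstaged to cN0, so palpable nodes are largely screened out before surgery. A node that is suspicious to touch, unstained, and in a patient with no stained node at all may be uncommon. At the protocol's 96%, about 6 of 147 patients per arm fail (0.04 × 147 = 5.9); rescue of 10-25% is then about one patient per arm. Section 1.1.3 also reports 99% detection with CNS in the group's earlier study, and both arms receive CNS. This stands: nothing in the documents supports r of 50% or more, and that row is an illustrative upper case.

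Second, section 5.4 is about what is removed and what follows, not about endpoint scoring. That is fair. It does not amend the definition in 5.2, but neither does it resolve the mismatch.

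Third, section 5.2 numbers SLNs at excision and section 5.5 requires numbering to carry through to the final pathology report, so a tracer-only analysis may be feasible from planned records. Possibly, but the protocol does not commit to recording tracer status node by node.

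A reader might go further than the text allows in four ways:
- That any failed mapping scores as a success. Only failures with a palpable suspicious node do.
- That the bias certainly favours non-inferiority. That requires the definition to cover both arms and a true deficit to exist.
- That an unstained UC node seen only on ultrasound would count. The UC text says suspicious nodes are excised, not that they are SLNs, and the only definition says palpable.
- That the instruction in section 5.4, "Prior to any pathological evaluation, confirmation of ex vivo counts per tissue should be conducted", makes matters worse. Its meaning is unclear for these tracers, but it does not feed the primary endpoint.

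**Conclusion.** The point holds on the wording. The sole SLN definition has a route that needs no tracer, the primary endpoint imposes no tracer condition, both arms remove suspicious nodes, and no other section corrects this. The arm-neutral wording makes application to both arms the natural reading, although its place under the control-arm heading leaves room for doubt.

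The effect on the error rate is conditional. With a true deficit at the margin and the definition applied to both arms, rescue of 10% of failures raises the false non-inferiority rate by about 2 to 3 points, and rescue of 25% brings it to 12.9-17.6%. With equal true rates and equal rescue there is no bias in the difference. Since r is an assumption and may be small, the documents do not support a claim that the trial's conclusion is unsafe. Severity: should-fix. Confidence is high on the wording and low on the effect size.

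**What to change.** - Move the SLN definition to a section that covers both arms, and reconcile sections 5.2, 5.4 and 6.3.2 with it.
- Define primary success as at least one excised lymph node that meets the tracer criterion: black in the UC arm, black and/or fluorescent in the GC arm.
- Record tracer status for each node at excision.
- Leave the removal of suspicious nodes as planned. Report unstained suspicious nodes separately, outside the identification rate and the SLN count.
- Report the current all-node definition as a sensitivity analysis.

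The cost is endpoint wording and one case report form field per node; all removed nodes already go to pathology. The planned 264 does not change, because the 96% assumption and the margin stay as they are. The downside is that both identification rates may come out slightly lower.

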**5.3 Reagents and Equipment**

- The dilution concentration of CNS (Lai Mei Pharmaceutical Co, Chongqing, China) is 50 mg/ml.
- The dilution concentration of ICG (Medical Pharmaceutical Co, Dandong, China) is 2.5 mg/ml.
- A fluorescence tracer system (Dipu Medical Technology Co., Ltd, Zhuhai, China) will be used to track subcutaneous lymph vessels and localized sentinel lymph nodes.
- An ultrasound diagnostic system (TOSHIBA APLIO 400, Japan) will be used for ultrasound positioning to locate lymph nodes.

CNSs and ICG will be obtained from commercial sources and stored according to the package insert instructions. The investigator is responsible for accounting for all trial drugs. Each time CNSs and ICG are dispensed to subjects enrolled in this study, the following information at a minimum will be recorded on the drug accessibility log: the patient’s subject number, manufacturer, and lot or batch number. At the completion or termination of the trial, a final drug accountability review and reconciliation must be completed, any discrepancies must be investigated and their resolution documented.

**5.4 Intra-operative Frozen Section of Lymph Nodes**

All removed lymph nodes will be sent for intraoperative frozen section analysis and pathology for further evaluation. Prior to any pathological evaluation, confirmation of ex vivo counts per tissue should be conducted. The pathological evaluation of the lymph nodes will include serial sectioning with H&E staining as well as IHC stain.

- In those cases in which intraoperative frozen section analysis is performed and all SLNs are found to be negative for malignancy on intraoperative frozen section evaluation, no further removal of axillary lymph nodes will be undertaken, unless otherwise determined as necessary at the discretion of the operating surgeon.
- In those cases in which intraoperative frozen section analysis is performed and the SLNs are determined to be positive for malignancy on intraoperative frozen section evaluation, a formal axillary lymph node dissection (levels I and II) may be performed at the discretion of the operating surgeon, or may be excluded at the discretion of the operating dissection (as based upon the ACOSOG Z0011 criteria).
- Any axillary lymph node that is neither “fluorescent” nor “black” but is determined to be intraoperatively clinically grossly suspicious (i.e., enlarged or hard) will also be removed. In those cases in which any clinically grossly suspicious lymph nodes removed intraoperatively are determined to be positive for malignancy on intraoperative frozen section evaluation, a formal axillary lymph node dissection may be performed at the discretion of the operating surgeon.
- In those cases in which no SLN can be intraoperatively identified at the time of the SLNB procedure, formal axillary lymph node dissection may be performed at the discretion of the operating surgeon.

**5.5 Postoperative Procedures**

All excised lymph nodes should undergo histopathological evaluation for the presence of tumors according to the current institutional standards. Final pathology results need to reflect consistent numbering and labeling from the intraoperative worksheets to the final report. SLNs need to be individually identified in the final pathology report.

Telephone follow-up 30 days post-operation will be conducted for adverse event assessment.

**6. STATISTICS**

**6.1 Randomization Methods**

Subjects who meet all inclusion and exclusion criteria will be enrolled in this study. Enrolled subjects will be randomized to one of two treatment groups: the UC group or the GC group. See Section 4 above for specifics on the randomization procedure.

**6.2 Study Populations**

The primary efficacy analysis will be carried out on the intent-to-treat population (ITT), which is defined as the population who underwent SLNB. The ITT analysis will be carried out for the identification rate, the median number of SLNs collected, the operative duration, and the intraoperative or postoperative complications.

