**2.2 Secondary Objectives**

- To compare the median number of SLNs collected;
- To compare the metastatic rate of SLNs, defined as the number of patients who have at least one positive SLN divided by the number of patients whose SLNs were identified;
- To compare the operative duration, defined as the time from skin incision to resection of the SLN specimens in patients with at least one SLN detected;
- To compare the intraoperative or postoperative complications.

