**6.3.1 Analysis of Baseline and Demographic Characteristics**

Baseline and demographic characteristics of the safe population will be summarized by treatment group and overall. Continuous variables will be summarized via the mean, median, standard deviation, minimum, maximum, and number of nonmissing observations. Categorical variables will be summarized via counts and percentages. The Chi-squared test or Fisher's exact test for categorical parameters and the t-test for continuous parameters will be applied to compare the two intervention groups. The results will be presented as the number of patients (%) or mean ± standard deviation (SD). P<0.05 is defined as statistical significance.

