**6.3.4 Safety Analyses**

The occurrence of any drug-related adverse events is not expected. The most likely drug-related adverse events include allergic reactions, local inflammatory reactions, and skin or fat necrosis.

An adverse event is any untoward, undesired, and/or unplanned clinical event in the form of signs, symptoms, disease, or laboratory testing, or physiological observations occurring in a human participating in a clinical study with a study drug, regardless of the causal relationship. This includes the following:

- Any clinically significant worsening of a preexisting condition.
- Any recurrence of a preexisting condition.
- An AE occurring from overdose of a study drug whether accidental or intentional.
- An AE occurring from abuse of a study drug.
- An AE that has been associated with the discontinuation of the use of a study drug.

A serious adverse event (SAE) is any AE occurring at any dose that results in one or more of the following outcomes:

- Death.
- Life-threatening situation.
- Inpatient hospitalization or prolongation of an existing hospitalization.
- Persistent or significant disability or incapacity.

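### Complications are compared only among patients who underwent SLNB, so a patient given tracer whose biopsy is then cancelled drops out of that comparison

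*Protocol*

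**What the plan says.** Section 6.2 names one analysis set, the ITT population, "which is defined as the population who underwent SLNB", and lists the endpoints to be analysed in it. The list ends with "the operative duration, and the intraoperative or postoperative complications". Complications are a between-arm secondary objective in section 2.2: "To compare the intraoperative or postoperative complications".

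Section 5.2 gives the order of events. In the UC group CNS is injected and then: "The injection site will be massaged for 15 minutes to promote drainage of the tracer into the axilla". The next step is again before surgery proper: "Before making the incision, ultrasound-guided exploration of the SLNs will be performed". The GC group has the same CNS injection and massage, followed by an injection of ICG and fluorescence imaging.

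Section 6.3.4 covers adverse events. It says drug-related events are not expected, and adds: "The most likely drug-related adverse events include allergic reactions, local inflammatory reactions, and skin or fat necrosis". Its definition of an adverse event covers any participant in a study with a study drug, whatever the cause. It names no analysis set.

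Section 6.3.1 refers to "Baseline and demographic characteristics of the safe population". That population is defined nowhere in the protocol and is used only for the baseline tables.

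**The concern.** A safety comparison should include everyone who was exposed. Here exposure starts at the tracer injection, but entry to the complications set depends on something that happens later, namely undergoing SLNB. A tracer reaction is one of the things that could prevent it. The rule can therefore remove a patient because of the event that the comparison is meant to count.

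The arms are also exposed differently: both receive CNS, and only the GC group receives ICG as well. A reaction to ICG that stopped the procedure could be lost from the GC group only.

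What is at stake is the complications comparison. This is a rule that the protocol states, not a detail left open for a statistical analysis plan.

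**Working it through.** **The plan's own figures.** Inputs from section 6.3.5: 96% identification in each group, margin 6 percentage points, one-sided α 0.05, power 80%, dropout 10%.

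- Per arm: n = (1.645 + 0.842)² × 2 × 0.96 × 0.04 / 0.06² = 131.9, rounded up to 132, so 264 in total. This matches the protocol.
- With dropout: 264 / 0.9 = 293.3, rounded up to 294, or 147 per arm as in section 3. This also matches.

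These figures concern the primary endpoint and do not change with the population used for complications. They supply only the 147 used below.

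**Tracing one patient through the text.** Take a patient who is injected with CNS, or with CNS and ICG, reacts before the incision and has the biopsy cancelled.

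| Section | Is she included? |
|---|---|
| 6.2, complications | No, on the literal wording: she did not undergo SLNB |
| 6.3.4, adverse events | Her event meets the definition, but no analysis set is named |
| 6.3.1, safe population | Cannot be decided: the set is undefined, and it serves baseline tables only |
| 6.3.6, missing values | Does not restore her: this rule only removes patients from analyses |

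**Effect on the reported rate.** Assume 147 injected in an arm, k reactions that cancel the biopsy, and no other complication. She leaves the numerator and the denominator together.

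| k | All injected | SLNB only |
|---|---|---|
| 1 | 1/147 = 0.7% | 0/146 = 0% |
| 2 | 2/147 = 1.4% | 0/145 = 0% |
| 3 | 3/147 = 2.0% | 0/144 = 0% |

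With 3 other complications and k = 1, the rates are 4/147 = 2.7% and 3/146 = 2.1%.

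Exact one-sided 95% upper bounds for k = 1 and no other complication:

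- 0/146: 1 − 0.05^(1/146) = 2.0%.
- 1/147: the rate p at which the probability of 0 or 1 events in 147 is 0.05, which is p = 3.2%.

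**How likely is such a case?** The protocol gives no rate, so r, the chance per patient of a reaction that cancels the biopsy, is an assumption. The expected number is 294 × r, and the chance of at least one among 294 patients is 1 − (1 − r)^294.

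| Assumed r | Expected among 294 | Chance of at least one |
|---|---|---|
| 0.05% | 0.15 | 14% |
| 0.1% | 0.29 | 25% |
| 0.5% | 1.47 | 77% |

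The only reaction rate in the protocol (section 1.1.1) is 1.8% for blue dye, of which about 23% are type I. That is 0.018 × 0.23 = 0.41%, or 0.6 per 147 patients. Blue dye is used in neither arm, and not every type I reaction would cancel a biopsy. The figure gives a scale, not an estimate.

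**The case against.** **Adverse events are not restricted.** A reader might infer that the patient disappears from the trial's safety data altogether. The documents do not support that. The section 6.3.4 definition has no SLNB condition and would capture her reaction, and section 7.4 requires serious events to be reported to the ethics committee. The list headed by allergic reactions belongs to section 6.3.4, not to the complications endpoint. This objection stands: only the complications comparison is shown to lose her.

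**Undergoing SLNB may begin at injection.** Injection and massage are the first steps of the mapping procedure in section 5.2, and section 5.4 uses SLNB for the procedure even when no node is found. On that reading she stays in. The reading is possible, but the protocol never says when SLNB begins, so the wording still needs settling.

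**The safe population suggests that a separate safety set was intended.** That is plausible, and its definition may stand in a statistical analysis plan that is not shown. Its absence alone would be no finding. But section 6.2 expressly places complications in the SLNB set, and an intended safety set elsewhere does not undo that.

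**Such events will be very rare.** Section 1.1.3 calls CNS nonallergic, section 1.1.2 describes ICG as safely used, section 3.2 excludes patients with known hypersensitivity to the tracers, and section 6.3.4 does not expect drug-related events. This stands, and it limits the weight of the point.

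**Conclusion.** The point holds for the complications endpoint. On its literal wording, section 6.2 makes membership of a safety comparison depend on an event after exposure that the tracer itself can influence, and no other section puts the patient back.

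The size is small. The likely number of affected patients is zero or one, and one such patient turns 0.7% into 0% in an arm. That rests on three assumptions: 147 injected per arm, the narrow reading of undergoing SLNB, and a rate of cancelling reactions that the protocol does not give. The identification-rate analysis does not depend on the set used for complications, and the sample size is unchanged.

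Two stronger readings should be resisted. First, a reader might conclude that the comparison is biased in favour of the GC group because only that group receives ICG. The rule permits unequal losses, but nothing in the documents shows that they would occur or how large they would be. Second, a reader might conclude that the baseline tables must move to all randomised patients. That does not follow from this defect.

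This is a clarification worth making before analysis. It does not threaten the trial's main conclusion.

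**What to change.** - In section 6.2, take complications out of the SLNB set and analyse them in all patients injected with CNS or ICG, grouped by tracers actually received.
- In section 6.3.4, name the same set for adverse events.
- Use that set as the definition of the safe population in section 6.3.1.
- State how a GC patient is shown if the procedure stops after CNS and before ICG. Grouped by tracers received, she counts as CNS only, so a note of her randomised arm keeps the table readable.

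The cost is a few lines of wording. Section 5.3 already requires a log by subject number each time CNS or ICG is dispensed, which helps to identify exposed patients. The sample size stays at 264, or 294 with dropout.

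There is one small added burden. The follow-up call in section 5.5 is timed at 30 days from the operation, so a patient whose operation is cancelled has no start date for it. Her call should be timed from injection; otherwise she could have no follow-up record and be removed again by the missing-value rule in section 6.3.6.
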